### Trial participants

Inclusion and exclusion criteria are described in full in Table 1. To be included in the trial, written informed consent from a parent/legal guardian will be required for each pediatric subject enrolled (every effort will also be made to gain written informed assent). In addition, pediatric subjects are to be otherwise healthy, aged 6 to < 12 years with a body weight ≥ 10 kg, have a positive rapid influenza diagnostic test which detects an antigen of influenza virus, and be judged by the investigator or sub-investigator to be able to take baloxavir tablet(s) and oseltamivir capsules or dry syrup. The main exclusion criteria are severe influenza symptoms requiring inpatient treatment, administration of systemic corticosteroids or immunosuppressive therapy, presence of an infectious disease requiring systemic antimicrobial therapy at the time of screening, allergies and/or a history of clinically problematic intolerance to anti-influenza drugs and/or acetaminophen, or a positive SARS-CoV-2 diagnostic test or suspected COVID-19 disease at the time of screening.

**Table 1 Tab1:** Inclusion and exclusion criteria

Inclusion criteria	
Age 6 to < 12 years	
Body weight ≥ 10 kg	
Diagnosed with influenza infection defined as: Fever (axillary temperature ≥ 38 °C) A positive RIDT by nasopharyngeal swab, pharyngeal swab, or nasal discharge At least one moderate or severe respiratory symptom (cough and nasal discharge/nasal congestion)	
Onset of first confirmed fever (≥ 37.5 °C) no more than 48 h before screening (Day 1)	
Judged by the investigator as able to take baloxavir tablet(s) and oseltamivir capsules or dry syrup	
Where possible, written informed assent from children Written informed consent from a parent or legal guardian	
Parents/guardians willing and able to comply with the trial requirements Patients who can comply with the trial requirements to the level of their understanding	
Exclusion criteria	
Severe influenza symptoms requiring hospitalization	
Risk factors for influenza infection including: Chronic respiratory diseases including uncontrolled bronchial asthma Hepatitis, liver cirrhosis Neurological disorders and neurodevelopmental disorders including brain, spinal, peripheral, and muscle disorders Endocrine disorders including diabetes, thyroid disease, and adrenal gland abnormalities Heart disease requiring drug treatment including congenital heart disease, congestive heart failure, and coronary artery disease	
Receiving systemic corticosteroids or immunosuppressive therapy	
Primary immunodeficiency syndrome	
Severe renal impairment (creatinine clearance < 30 mL/min or eGFR < 30 mL/min/1.73 m^2^)	
Human immunodeficiency virus infection	
Malignant disease within the past 5 years	
Disorders of consciousness including abnormal behavior^a^ and convulsions, and complicated by encephalitis/encephalopathy	
History of encephalitis/encephalopathy or epilepsy not controlled with antiepileptic drugs or abnormal behavior^a^ associated with influenza infection in the past 2 years	
Infectious diseases requiring systemic antimicrobial therapy and/or antiviral medicine (except anti-influenza medicine) at screening	
Considered by the investigator to be using prohibited drugs	
Receiving baloxavir, amantadine, or NAIs (oseltamivir, zanamivir, peramivir, and laninamivir) within 30 days before screening	
History of allergies to anti-influenza drugs, or acetaminophen, or clinically problematic intolerance	
Positive SARS-CoV-2 or suspected COVID-19 disease	
Any underlying disease that may affect study outcomes	
Difficulty collecting blood from a vein Patients received an investigational or unapproved drug within 30 days or 5 half-lives, whichever is longer, before screening Patients with diseases or conditions which, in the opinion of the investigator, may make it difficult to ensure patient safety or study data quality Patients who, in the opinion of the investigator, are inappropriate for participation in the study Female patients who has experienced menarche and who are pregnant, plan to become pregnant during the study period, or are breastfeeding	

^a^Actions such as a sudden start, jump, or any other unexpected behavior that may be life-threatening

*COVID-19* coronavirus disease 2019; *eGFR* estimated glomerular filtration rate; *NAI* neuraminidase inhibitor; *RIDT* rapid influenza diagnostic test; *SARS-CoV-2* severe acute respiratory syndrome coronavirus 2

### Treatment protocol

Eligible pediatric subjects will receive a single oral dose of baloxavir tablet at the approved dose in Japan (10 mg for children weighing ≥ 10 to < 20 kg, 20 mg for ≥ 20 to < 40 kg, and 40 mg for ≥ 40 kg) [30] on Day 1 or oral oseltamivir capsules or dry syrup (2 mg/kg for subjects weighing < 37.5 kg, 75 mg for ≥ 37.5 kg) twice daily on Days 1–5 (Fig. 1). If subjects skip a dose, the dose will be taken as soon as they are aware of missing a dose unless the next dose is within 2 h. The subjects will be allowed to use acetaminophen (≤ 60 mg/kg/day or < 1500 mg/day, which is the maximum dose for adults) as needed throughout the trial for the alleviation of severe symptoms. Pediatric subjects or their parent/guardian will record the date and time of the use of acetaminophen using an electronic patient-reported outcome (ePRO) diary.

The following drugs or treatments will be prohibited during the trial: systemic antiviral drugs, antibacterial or antifungal drugs (except for suspected bacterial or fungal infection after administration of study drug), antipyretic analgesics (except acetaminophen), injection or oral corticosteroids (inhalant is acceptable), immunosuppressive drugs, and warfarin.

### Clinical and laboratory monitoring

Eligible subjects will undergo a confirmatory test for influenza A or B at the screening visit on Day 1. To be included in the primary analysis population, influenza virus infection will be confirmed by reverse transcription-polymerase chain reaction (RT-PCR). A full description of the visit and assessment schedule is provided in Table 2. The following outcome measures will be assessed by subjects or their parent/guardian and recorded in an ePRO diary from postdose Day 1 to postdose Day 9: influenza symptom severity and body temperature (axillary) using an electronic thermometer taken right before or at least 4 h after administration of acetaminohen, if relevant; the severity of seven influenza symptoms (cough, sore throat, headache, nasal discharge/nasal congestion, feverish or chills, muscle ache or joint pain, and fatigue) will be assessed by subjects ≥ 7 years who are deemed able to assess influenza symptoms themselves; the severity of two influenza symptoms (cough, nasal discharge/nasal congestion) will be assessed by a parent/guardian for subjects < 7 years and/or those ≥ 7 years who are considered by the investigators to not able to assess influenza symptoms themselves.

**Table 2 Tab2:** Visit and assessment schedule

Day	1		2 +1 day	3	4	5 -1 to +2 days	6	7	8	9	10 −1 to +4 days 4	Discontinuation +14 days
Visit	1^a^		2			3						
	Pre dose	Post dose										
Informed consent	X											
Inclusion/exclusion criteria	X											
Demographics, clinical characteristics, and medical history	X											
Enrollment and randomization	X											
Baloxavir administration		X										
Oseltamivir administration		X	X	X	X	X						
Diary (ePRO)												
Body temperature	X	X^a^	qid		bid							
Influenza symptom severity	X	X^a^	bid									
Medical examination^b^	X		X			X					X	X
Vital signs	X		X			X					X	X
Influenza RIDT	X^c^											
SARS-CoV-2 test	X^d^		X^e^									
Influenza virus tests (RT-PCR, titer, RNA, PA, or NA sequence)	X		X			X					X	X
Influenza virus serum antibody titer test (HI method)	X											
Intrahousehold influenza infection rate questionnaire											X	X
TEAE reporting	X	X	X	X	X	X	X	X	X	X	X	X

X denotes assessment to be undertaken

*bid* twice a day; *COVID-19* coronavirus disease 2019; *ePRO* electronic patient-reported outcome; *HI* hemagglutination inhibition; *NA* neuraminidase; *PA* polymerase acidic protein; *qid* four times a day; *RIDT* rapid influenza diagnostic test; *RT-PCR* reverse transcription-polymerase chain reaction; *SARS-CoV-2* severe acute respiratory syndrome coronavirus 2; *TEAE* treatment-emergent adverse event

^a^Not measured if study drug taken after 18:00

^b^Participants’ height and body weight are measured on Day 1 (predose/screening)

^c^Participants who have an RIDT and/or other influenza virus test within 48 h of symptom onset but before written informed consent do not need to take an RIDT and/or other influenza virus test on Day 1

^d^Participants who are determined to be SARS-CoV-2 negative according to the COVID-19 clinical guideline in Japan (https://www.mhlw.go.jp/content/000712473.pdf) before giving written consent do not need to undergo a SARS-CoV-2 test on Day 1

^e^This test will be conducted according to the COVID-19 clinical guideline as appropriate

The presence of SARS-CoV-2 infection will be assessed using an approved rapid SARS-CoV-2 test which includes but not limited to SARS-CoV-2 antigen test. For influenza virology tests, nasopharyngeal swabs will be tested for influenza virus type/subtype, viral RNA load and infectious influenza virus titer, and amino-acid substitutions in the PA protein subunit and neuraminidase (NA) using Sanger sequencing and a nested PCR (LSI Medience Corporation, Tokyo, Japan), as previously described [27]. Medical examinations will be conducted by investigators, and vital signs will be measured by investigators, nurses, or medical technicians, as appropriate.

For the intrahousehold (cohabitants or family members who live together) influenza virus transmission rate, household members who give their written consent will be provided with a paper questionnaire on Day 1 (predose). Completed questionnaires will be collected on Day 10. The questionnaire covers information on the following: household size (including age category); the number of household members infected from the pediatric subject’s enrollment up to Day 10 or until discontinuation from the study; and the date of each household member’s diagnosis of influenza infection, use of anti-influenza drug therapies, and the date of their recovery of normal body temperature (< 37 °C).

### Outcome measures and endpoints

The primary clinical endpoint is the time to illness alleviation (TTIA), defined as the time from baloxavir or oseltamivir administration until the following criteria were reached and sustained for at least 21.5 h (24 h—10%): both cough and nasal discharge/nasal congestion assessed as 0 (absent) or 1 (mild) and axillary temperature less than 37.5 °C (Table 3).

**Table 3 Tab3:** Outcome measures and endpoints

Efficacy	
Primary clinical endpoints	
Time to illness alleviation of influenza, defined as the time from baloxavir or oseltamivir administration until the following criteria were reached and sustained for at least 21.5 h (24 h—10%): both cough and nasal discharge/nasal congestion assessed as 0 (absent) or 1 (mild) and axillary temperature less than 37.5 °C	
Secondary endpoints	
Time to sustained resolution of influenza symptoms (cough, nasal discharge/nasal congestion) rated using the Influenza Symptom Severity Scale as absent (grade 0) or mild (grade 1) and resolution of fever (normal body temperature < 37.5 °C) for at least 72 h	
Time to resolution of fever (< 37.5 °C) for at least 12 h	
Time to sustained resolution of fever for at least 72 h	
Proportion of subjects with resolution of fever at each time point	
Time to resolution of all seven influenza symptoms (cough, sore throat, headache, nasal discharge/nasal congestion, feverish or chills, muscle ache or joint pain, and fatigue), rated using the Influenza Symptom Severity Scale as absent (grade 0) or mild (grade 1) for at least 21.5 h	
Time to resolution of each influenza symptom for at least 21.5 h	
Incidence of influenza-related complications (pneumonia determined by X-ray, bronchitis, sinusitis, otitis media)	
Incidence of influenza-related complications seen particularly in children (influenza-associated encephalitis or encephalopathy, febrile seizures, myositis) Incidence of death and hospitalization from influenza-related complications or influenza-related complications seen particularly in children	
Use of antibiotics	
Virological endpoints Infectious influenza virus titer and the amount of virus RNA (determined by RT-PCR) at each time point Change from baseline in infectious influenza virus titer and amount of virus RNA (determined by RT-PCR) at each time point Proportion of participants whose influenza virus titer and quantitative RT-PCR are above and below the lower limits of quantification at each time point Time to the first cessation of viral shedding based on the influenza virus titer, defined as the time postdose until virus titers reach the lower limit of quantification for the first time Time to sustained cessation of viral shedding based on influenza virus titer, defined as the time from the last positive virus titer postdose to the first virus titer that is below the lower limit of quantification	
Exploratory endpoints	
Emergence of amino-acid substitutions (PA/I38X and NA/H275Y) in subjects who are RT-PCR positive for influenza infection pre- and postdose. Treatment-emergent influenza virus substitutions in PA/I38 or NA/H275 will be defined as amino-acid substitution occurring between Day 1 and the last time point where the influenza virus RT-PCR cycle threshold is < 31 for the H1 subtype or < 29 for the H3 subtype Rate of intrahousehold influenza infection	
Safety	
AEs, AEs possibly related to baloxavir or oseltamivir, SAEs, vital signs	

*AE* adverse event; *NA* neuraminidase; *PA* polymerase acidic protein; *RT-PCR* reverse transcription-polymerase chain reaction; *SAE* serious adverse event

The main secondary endpoints include the time to sustained resolution of influenza symptoms (cough, nasal discharge/nasal congestion, and body temperature) for at least 72 h; the time to resolution of fever (normal body temperature < 37.5 °C) for at least 12 h; the time to sustained resolution of fever for at least 72 h; the proportion of subjects with resolution of fever at each time point; the time to resolution of seven influenza symptoms (cough, sore throat, headache, nasal discharge/nasal congestion, feverish or chills, muscle ache or joint pain, and fatigue) for at least 21.5 h; the incidence of influenza-related complications and those influenza-related complications seen particularly in children (influenza-associated encephalitis or encephalopathy, febrile seizures, myositis); the use of antibiotics for treatment of infectious disease secondary to influenza infection; and the change from baseline in infectious influenza virus titer.

The assessment of the safety and tolerability of study drugs will include the frequency and nature of adverse events (AEs), AEs related to study drugs, SAEs, and vital signs. All AEs will be managed in accordance with good medical practice by the participating physicians as appropriate. An AE will be considered “serious” if it results in death, is life-threatening, requires hospitalization or prolongation of hospitalization, or is persistent or results in significant incapacity or substantial disruption to daily life. All deaths and immediately life-threatening events, whether related or unrelated to study drug, will be reported to the CRB as soon as possible. All SAEs will be shared with all investigators participating in the study. If there is a reasonable possibility that the study procedure causes an unanticipated SAE, the sponsor of the study will report the SAE to the Pharmaceuticals and Medical Devices Agency in Japan.

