### Statistical analysis

The planned sample size is 200 pediatric subjects with influenza (134 in the baloxavir treatment group and 66 in the oseltamivir treatment group). Because of the anticipated challenges in enrolling patients during the COVID-19 pandemic and because the study is not designed to demonstrate noninferiority or superiority considering feasibility, no formal statistical sample-size calculations will be performed. The intention-to-treat infected population for efficacy will include all subjects who receive at least one dose of baloxavir or oseltamivir and who have a confirmed diagnosis of influenza virus infection by RT-PCR on Day 1. Based on our past experience in clinical studies in Japan [27, 28], it is expected that almost all subjects with a positive rapid influenza diagnostic test be confirmed for influenza by RT-PCR. The safety population will consist of all subjects who receive at least one dose of baloxavir or oseltamivir. Statistical analysis will be based on descriptive statistics and no statistical tests will be used.

For the primary endpoint, the median TTIA (95% confidence interval [CI]) will be assessed using Kaplan–Meier curves for each treatment group, and the efficacy of baloxavir compared with oseltamivir will be assessed using between-group differences (95% CI). As a secondary analysis, the restricted mean survival time (RMST) and 95% CI up to Day 9 will be estimated for each treatment group by direct integration of the Kaplan–Meier survival curve. The between-group difference in RMST (95% CI) will also be calculated. The secondary time-to-event efficacy analyses will be assessed in the same manner as the primary analysis for the primary endpoint. For all other analyses, quantitative data will be summarized by descriptive statistics (mean, standard deviation [SD], maximum, median, minimum) and the mean between-group difference (95% CI). Qualitative data will be summarized by frequency, proportion, and the between-group difference in proportion (95% CI) using the Santner and Snell method.

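### The titer-based cessation endpoints set no baseline-titer condition, so a child with no quantifiable virus predose or at Day 2 counts as having stopped shedding

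*Protocol article*

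**What the plan says.** Table 3 of the protocol article (Outcome measures and endpoints) places two titer-based cessation endpoints among the secondary efficacy endpoints:

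- First cessation is "defined as the time postdose until virus titers reach the lower limit of quantification for the first time".
- Sustained cessation is "defined as the time from the last positive virus titer postdose to the first virus titer that is below the lower limit of quantification".

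The Statistical analysis section gives one efficacy population, made up of dosed children "who have a confirmed diagnosis of influenza virus infection by RT-PCR on Day 1". It contains no titer criterion. On method, "The secondary time-to-event efficacy analyses will be assessed in the same manner as the primary analysis for the primary endpoint", which means Kaplan–Meier medians and a between-group difference with 95% CI. As a secondary analysis of the primary endpoint, "the restricted mean survival time (RMST) and 95% CI up to Day 9 will be estimated for each treatment group".

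The Table 2 row "Influenza virus tests (RT-PCR, titer, RNA, PA, or NA sequence" is scheduled at Day 1 predose, Day 2 (+1 day), Day 5 (−1 to +2 days), Day 10 (−1 to +4 days) and discontinuation. Table 3 does narrow one virological endpoint to a subset: amino-acid substitutions are assessed "in subjects who are RT-PCR positive for influenza infection pre- and postdose". The titer endpoints carry no such limit.

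**The concern.** RT-PCR detects viral RNA, while the cessation endpoints use infectious titer. The article treats RNA load and titer as separate measurements, so a positive RT-PCR does not guarantee a quantifiable titer. A child below the limit predose and still below it at Day 2 shows no measurable shedding that treatment could stop. Read literally, the definition still records an event at the Day 2 swab in either arm.

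The sustained definition has a gap of its own. Its clock starts at the last positive postdose titer. A child with no positive postdose titer has no start, and so no value.

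What is at stake is how the virological comparison reads. The Discussion cites a shortening of about 24 h in median time to cessation in the earlier pediatric trial, so readers will look at this result.

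**Working it through.** **The plan's own figures.** The article states that no formal sample-size calculation was made, so only the split can be checked. 200 × 2/3 = 133.3 and 200 × 1/3 = 66.7, consistent with 134 and 66. The article gives neither the share of children below the titer limit at baseline nor the limit itself.

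**Model.** Let p0 be the fraction that is RT-PCR-positive, below the limit predose and still below it at Day 2. It is assumed equal in both arms. Let q be the proportion of the remaining children who have cleared by a given swab.

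- Observed proportion cleared = p0 + (1 − p0)q
- Between-arm difference = (1 − p0)(q_B − q_O), where B is baloxavir and O is oseltamivir

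**Assumed inputs (none from the article).** Clearance by Day 2 is 60% (baloxavir) against 25% (oseltamivir). By Day 5 it is 85% against 75%, and by Day 10 it is complete. Nominal swab times are 24, 96 and 216 h, with restriction at 216 h. Restricted mean = 24 + 72(1 − q at Day 2) + 120(1 − q at Day 5). With p0 = 0, the difference is 72 × 0.35 + 120 × 0.10 = 37.2 h.

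| p0 | Children affected (of 134 / of 66) | Day 2 difference, points | Restricted-mean difference, h |
|---|---|---|---|
| 0 | 0 / 0 | 35.0 | 37.2 |
| 5% | 6.7 / 3.3 | 33.3 | 35.3 |
| 10% | 13.4 / 6.6 | 31.5 | 33.5 |
| 20% | 26.8 / 13.2 | 28.0 | 29.8 |

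Both differences shrink by exactly 1 − p0.

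**The planned measure: difference in medians.** An arm's median falls at the Day 2 swab once p0 + (1 − p0)q reaches 0.5, that is, once q reaches (0.5 − p0)/(1 − p0). This is 47%, 44% or 38% at p0 = 5%, 10% or 20%, instead of 50%. Whether the median difference changes depends on which arm crosses that threshold. At p0 = 10%, with the same Day 5 rates:

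- Day 2 clearance 60% against 25%: observed 64.0% and 32.5%. The median difference stays at 72 h (24 against 96 h), as it does for every p0 examined up to 20%.
- 60% against 45%: observed 64.0% and 50.5%. Both medians are at 24 h, so the difference falls from 72 h to 0.
- 47% against 25%: observed 52.3% and 32.5%. The baloxavir median moves from 96 to 24 h, so the difference rises from 0 to 72 h.

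For comparison, if clearance were observed continuously and were exponential, a 24 h difference in medians would be multiplied by 1 + log2(1 − p0). That gives 22.2, 20.4 or 16.3 h at p0 = 5%, 10% or 20%. The trial's swab grid does not behave this smoothly.

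**Sustained cessation.** The undefined group is every child with no positive postdose titer. It includes baseline-positive children who are below the limit at Day 2 and stay there. Under the assumed rates with p0 = 0, that is at most 0.60 × 134 = 80.4 and 0.25 × 66 = 16.5 children. A baseline restriction alone therefore does not close this gap.

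**The case against.** The strongest reply is that this is a condensed article. A subset for particular endpoints is often set in the analysis plan, which is not shown. A reader might infer that the analysis will certainly be run without a baseline-titer condition, and the documents do not prove that. What stands is that the article states both a population and an endpoint rule, narrows a neighbouring endpoint in the same table, and leaves these two unrestricted. Applied as written, the rule gives the wrong answer for these children.

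A reader might also infer that such children dilute the planned comparison. That is certain only for proportions and restricted means, and only if p0 is above zero. The restricted mean is described for the primary endpoint, and its use for these endpoints is not clearly stated. The planned median difference can move either way or not at all.

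A low baseline titer alone does not produce an automatic event. A poorly swabbed child may be shedding and have a quantifiable titer at Day 2. Only a second result below the limit triggers the event, and the restriction would leave out some such shedders.

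Nor does chance imbalance pass straight into the comparison. The standard error of the between-arm difference in p0 is √[p0(1 − p0)(1/134 + 1/66)], or 3.3 and 4.5 points at p0 = 5% and 10%. It enters weighted by the uncleared share (0.40 and 0.75 under the assumed rates). It is ordinary sampling variation, which the confidence interval reflects.

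The size is probably small. Table 1 requires fever of at least 38 °C, a positive rapid antigen test and fever onset within 48 h. At p0 = 5% the Day 2 shift is 1.7 points. The 95% half-width for 60% against 25% is about 1.96 × √(0.24/134 + 0.1875/66) = 13.3 points. The planned by-visit proportions above and below the limit would also show baseline negatives by arm, if predose counts as a time point. Restricting that by-visit proportion would be a matter of preference.

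**Conclusion.** The point holds in a limited form. As written, both cessation endpoints apply to an RT-PCR-defined population without a quantifiable predose titer. Under first cessation, a child below the limit predose and at Day 2 is scored as ceasing at Day 2. Under sustained cessation, any child with no positive postdose titer has no defined value.

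Attenuation of proportions and restricted means by 1 − p0 follows from the model: 35 points become 33.3 or 31.5 at p0 = 5% or 10%. It rests on equal p0 in the arms and on assumed clearance rates. The effect on the planned median difference is unpredictable in direction. No test is planned, the endpoints are secondary, and time to cessation is not in the text's list of main secondary endpoints. No error rate, sample size or primary result is affected, so the priority is modest.

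**What to change.** - Analyse the two time-to-cessation endpoints in RT-PCR-positive children whose predose Day 1 titer is at or above the lower limit of quantification.
- Report by arm how many children this leaves out, and keep the analysis of all infected children as supportive.
- Redefine sustained cessation so that it has a value for a child with no positive postdose titer. One way is to time it from dosing to the first titer below the limit that is not followed by a titer at or above it.

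The cost is a few lines in the endpoint table and analysis plan. The predose titer is already scheduled. The subset is fixed before dosing, so the comparison remains randomised. The downside is a somewhat smaller denominator for these two endpoints.

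### Table 3 starts the clock for time to sustained cessation of viral shedding at the last positive swab and not at dosing, so the literal value is a gap between two visits

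*Protocol article*

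**What the plan says.** Table 3 (Methods, Outcome measures and endpoints) lists two time-to-event virology endpoints next to each other.

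- Time to first cessation is "defined as the time postdose until virus titers reach the lower limit of quantification for the first time".
- Time to sustained cessation is "defined as the time from the last positive virus titer postdose to the first virus titer that is below the lower limit of quantification".

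The primary endpoint in the same section is "defined as the time from baloxavir or oseltamivir administration until the following criteria were reached and sustained". No other part of the article gives sustained cessation a dosing origin.

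Table 2 (Clinical and laboratory monitoring), in the row "Influenza virus tests (RT-PCR, titer, RNA, PA, or NA sequence", schedules swabs before dosing on Day 1, then on Days 2, 5 and 10 and at discontinuation. The visit windows are +1 day for Day 2, −1 to +2 days for Day 5 and −1 to +4 days for Day 10.

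On analysis, the Statistical analysis section says: "The secondary time-to-event efficacy analyses will be assessed in the same manner as the primary analysis for the primary endpoint". That means Kaplan–Meier medians and a between-group difference with a 95% confidence interval.

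**The concern.** A time to cessation should say how long after treatment a child goes on shedding virus. The sentence for sustained cessation states both a start and an end, and the start is the last positive swab. The interval it defines is the stretch between two neighbouring swabs within which clearance happened. It is not the time taken to clear.

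Three things follow.

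- The value is set mainly by visit spacing.
- A child who is already below the lower limit of quantification (LLOQ) at Day 2 and stays there has no start point, so the fastest clearers have no value.
- If one arm clears faster, it has more such children, and the children left for comparison are no longer the randomized groups.

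Virological efficacy is a stated aim of the trial. The Discussion reports that an earlier pediatric trial found a median time to cessation of shedding about 24 h shorter with baloxavir. An endpoint that cannot register a difference of that kind would mislead if reported at face value.

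This is a stated definition and not a detail left to an analysis plan. A plan that copies the sentence copies the problem.

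**Working it through.** **Inputs.** The start and end of the endpoint come from Table 3, and the swab days and windows from Table 2. No sample-size, power or alpha figure depends on this endpoint ("no formal statistical sample-size calculations will be performed"), so the plan has no figure of its own to reproduce.

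**Step 1: list every swab pattern.** Take + as positive and − as below the LLOQ on Days 2, 5 and 10 at nominal days, with no swab missed.

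- As written, reading A: (first negative *after* the last positive) − (last positive).
- As written, reading B: (first negative *of all*) − (last positive).
- Dosing-based: (first negative after which no later titer is positive) − Day 1.

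| Days 2, 5, 10 | Reading A | Reading B | Dosing-based |
|---|---|---|---|
| − − − | no value | no value | 2 − 1 = 1 day |
| + − − | 5 − 2 = 3 days | 3 days | 5 − 1 = 4 days |
| + + − | 10 − 5 = 5 days | 5 days | 10 − 1 = 9 days |
| − + − | 10 − 5 = 5 days | 2 − 5 = −3 days | 9 days |
| + − + | no value | 5 − 10 = −5 days | censored |
| − + +, − − + | no value | 2 − 10 = −8 days | censored |
| + + + | no value | no value | censored |

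Under reading A only two values can occur, 3 and 5 days, and both are visit spacings. Under reading B every rebound pattern gives a negative time.

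**Step 2: apply the windows.** Day 2 can fall on Days 2–3, Day 5 on Days 4–7 and Day 10 on Days 9–14.

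- The Day 2 to Day 5 gap can be 4 − 3 = 1 to 7 − 2 = 5 days.
- The Day 5 to Day 10 gap can be 9 − 7 = 2 to 14 − 4 = 10 days.

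The timing of visits within their windows therefore moves the value as much as the virus does.

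**Step 3: illustrate the effect on a comparison.** The documents give no shedding-time distribution, so what follows is assumed: lognormal shedding time, log-SD 0.5, no rebound. Nominal swabs fall 24, 96 and 216 h after dosing.

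The share with no positive titer after dosing is Φ(ln(24/m)/0.5) for true median m:

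- m = 24 h: Φ(0) = 50%
- m = 48 h: Φ(−1.386) = 8%
- m = 72 h: Φ(−2.197) = 1%

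| True medians | Visits | As written, children with a value | Undefined |
|---|---|---|---|
| 48 vs 72 h | nominal | 72 vs 72 h | 8% vs 1% |
| 48 vs 72 h | uniform over windows | 79 vs 88 h | 28% vs 9% |
| 24 vs 48 h | nominal | 72 vs 72 h | 50% vs 8% |
| 24 vs 48 h | uniform over windows | 76 vs 79 h | 76% vs 28% |

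**Step 4: give the corrected endpoint the same test.** For true medians of 48 vs 72 h, the dosing-based version gives 96 vs 96 h at nominal visits and about 99 vs 120 h across the windows. A true difference of 24 h thus appears as follows.

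- Nominal visits: 0 h as written and 0 h corrected.
- Across the windows: 88 − 79 = 9 h as written and about 120 − 99 = 21 h corrected.

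**Step 5: try a different shape.** Assume exponential shedding and nominal visits. The undefined share is 1 − 2^(−1/m), with m in days.

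| True median (days) | As-written median (days) | Undefined | Dosing-based median (days) |
|---|---|---|---|
| 1 | 3 | 50% | 1 |
| 1.5 | 3 | 37% | 4 |
| 2.5 | 3 | 24% | 4 |
| 4 | 3 | 16% | 4 |
| 6 | 5 | 11% | 9 |

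The as-written median stays at 3 days while the true median goes from 1 to 4 days.

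**The case against.** The strongest reply is that this is a wording slip of small consequence. The intended meaning is probably dosing to the first negative titer after the last positive one. The trial is descriptive, with no tests and no sample-size calculation. This endpoint is outside the list of main secondary endpoints in the text, where the only virology measure is change from baseline in titer. All of that stands, and it sets the weight of the point. It does not repair the sentence, which taken literally still produces visit gaps.

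Several stronger readings are tempting, and the documents do not support them.

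- *The value has nothing to do with shedding.* Shedding decides whether the 3-day or the 5-day gap is scored, so the value is not wholly independent of it.
- *Rebound gives negative times.* This holds only if *first* means the first negative of all. In an endpoint that runs from the last positive, the first negative after it is the more natural reading, and it cannot be negative.
- *The trial cannot show faster clearance.* First cessation is counted from dosing. Titer, RNA, change from baseline and the proportion above and below the LLOQ are also reported at each time point. What is lost is the version that is sensitive to rebound.
- *The definition alone hides a difference between arms.* Three swabs after dosing do part of that. At nominal visits the corrected endpoint also gives equal medians for 48 vs 72 h.
- *Fast clearers are excluded by rule.* The article does not say so. The text leaves them without a value, and their handling may be settled in an analysis plan that is not shown.
- *Viral clearance is the main advantage expected of baloxavir.* The Discussion reports the shedding result of the previous pediatric trial but does not rank it.

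**Conclusion.** Wrong as written, and below must-fix. That the literal endpoint is a visit gap, nominally 3 or 5 days, and is undefined without a positive titer after dosing follows from Tables 2 and 3 and needs no assumption beyond complete scheduled swabs. That more children would be undefined in the faster-clearing arm follows if the arms do differ in clearance.

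The size of the masking is less certain. In the scenarios run, a true 24 h difference in medians showed as 0 to 9 h, with undefined shares that differed between arms by 7 to 48 percentage points (8 − 1 and 76 − 28). Those figures rest on assumed medians, an assumed log-SD, no rebound and an assumed spread of visits within the windows.

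**What to change.** Replace the definition in Table 3, and in the analysis plan if it repeats it, along these lines: time from first dose of study drug to the first titer below the LLOQ after which no later titer is positive. Add two rules.

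- Children below the LLOQ from Day 2 onward count as events at that swab.
- Children who never meet the definition are censored at their last swab.

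This brings the endpoint into line with first cessation and the primary endpoint, gives every child with a swab after dosing an event or a censoring time, and removes the ambiguity over *first*. It costs one sentence plus the two rules and needs no new data or visits. It should be settled before the analysis. Any report should say that with swabs on Days 2, 5 and 10 the time is known only to within a visit interval.
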